### Intervention

The intervention has been described in full in a manual developed for the purposes of this study and has been informed by existing manuals for group songwriting [44], individual psychodynamic music therapy for depression [30, 47] and principles of resource-oriented music therapy [48]. The intervention was developed through focus group discussions with music therapists, psychologists and service users with a diagnosis of depression and was finalised in team discussions with music therapists and Heads of Arts Therapies involved in the study. The Template for Intervention Description and Replication [63] and Standard Protocol Items: Recommendations for Interventional Trials (SPIRIT) [64] checklists are attached as Additional files 1 and 2. The intervention manual and full study protocol are available on request from the authors.

Group music therapy will be provided three times per week over 14 weeks by two HCPC-registered music therapists. Each session will last 90 minutes and will comprise warm-up activities moving to sharing of pre-known songs and improvisation. Therapists will move from improvisation into songwriting, which will then be the main focus for the remainder of the session. Opportunities will be offered after each activity for verbal reflection. The last 15 minutes will be dedicated to reviewing the session and may include playing through a final piece of music.

The intervention will be provided in a community centre within the locality of Newham. The community centre is a non-NHS site and offers facilities for additional social contact such as a café and wider non-medical community groups. Music therapists will receive weekly clinical supervision from the chief investigator.

### Wait-list control

The wait-list control group will receive treatment as usual whilst study measures are completed and will then be eligible to receive group music therapy once the 6-month follow up has been completed. Receipt of services will be assessed throughout this time in both arms to enable an initial description of the types of services received and associated cost.

### Criteria for discontinuation

Participants will be withdrawn from the intervention if the participant becomes too unwell to continue due to loss of capacity to consent to group attendance, if the patient has a level of risk assessed by the clinical team to require hospitalisation or if music therapists and the clinical team determine that the patient’s current mental state, behaviour or risk to self or others requires discontinuation of the intervention. Reasons for withdrawal will be documented as part of feasibility measures.

### Randomisation

Randomisation will occur once all 30 participants have been recruited and baseline measures have been completed. In order to obtain sufficient data on the intervention, we will utilise simple block randomisation with unbalanced allocation so that 20 participants receive the intervention and 10 are allocated to the wait-list control group. A researcher independent of the study team will perform the randomisation using the Experimental Design Generator and Randomiser (EDGAR-II) [65] and inform the music therapists and unblinded member of the study team of the allocation by email. The music therapists will then inform participants of their allocation and provide additional support if required.

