### Estimation and appropriateness of outcomes

We expect to see changes in a range of clinical and social outcomes. However, we do not yet know which measures might be most appropriate in terms of acceptability of completion and variability of outcome. Our proposed primary outcome is symptoms of depression, measured by an observer-rated scale (Montgomery-Åsberg depression rating scale [62]). We will also measure potential changes in self-rated depression, social functioning, psychological distress, self-esteem, self-efficacy, mood, relationships, satisfaction with treatment, work and social adjustment, quality of life and service use. We will examine the acceptability and provide descriptive statistics and estimates of effect of the proposed outcome measures to inform the design of a future randomised controlled trial. As we are providing a group intervention, we also plan to estimate the intra-cluster correlation coefficient to take this into account in conjunction with future sample size calculations. To aid estimation of the cost of the intervention, we plan to conduct a preliminary economic analysis to estimate the cost of services received by the intervention and control groups.

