### Aims and objectives

The study aims to pilot group music therapy for patients with long-term depression and assess the feasibility of conducting a larger randomised controlled trial. The results will inform the design of future studies, the refinement of the manual and training of music therapists. Should the trial be found feasible, a protocol will be produced for a full-scale randomised controlled trial.

The objectives are to:Assess the acceptability of the methodology to professionals and patientsAssess the feasibility of recruitment processesIdentify the number of eligible participants, participant rates and retention ratesAssess the researcher time and costs per participantAssess the appropriateness of outcome measures, data on the variability of the outcome for sample size calculation, an estimate of the control group mean to ensure change is feasible and the intra-cluster correlation coefficientAssess the intervention in terms of testing components, measuring adherence and estimating the likely intervention effectAssess the exact cost of delivery of group music therapy and the services received

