### Outcome measures and endpoints

Our primary interest is in the feasibility of the trial design and intervention. A summary of the main feasibility outcomes, success criteria and timing is shown in Table 1. Proposed clinical outcomes are:

**Table 1 Tab1:** Methods and timing for assessing, recording and analysing outcome parameters

Outcome	Method	Success criteria				Timing
		Stop	Continue, modify protocol	Continue without modification but monitor closely	Continue without modifications	
Acceptability of methodology	Recruitment and retention rates as below					End of recruitment (week 8)
	Compliance	Mean attendance <10 sessions	Mean attendance <14 sessions	Mean attendance 14 sessions	Mean attendance 14+ sessions	End of intervention (week 22)
	End interviews	Unfavourable views, serious concerns	Unfavourable views, suggestions for modification	Favourable views, suggestions for modification	Favourable views, no concerns	1 month post-intervention (week 26)
Feasibility of recruitment processes	Screening rates	Identify <50 potentially eligible subjects	Identify <100 potentially eligible subjects	Identify 100–128 potentially eligible subjects	Identify >128 potentially eligible subjects	End of recruitment
	Recruitment rates	Recruit <50% of sample size	N <25 in 8wks, <5% per week	*N* = 25–30 in 8wks, <13% per week	*N* = 30 in 8wks, 13% per week or greater	End of recruitment
	Participation rates	Participation rate <5%	Participation rate 5–15%	Participation rate 15–25%	Participation rate 25% or greater	6 months post-intervention
	Retention rates	Attrition >75%	Attrition 50–75%	Attrition 30 − 50%	Attrition <30%	6 months post-intervention
	End interviews	N/A	Major suggestions to improve recruitment processes	Minor suggestions to improve recruitment processes	No suggestions to improve expressed	1 month post-intervention (week 26)
Identify number of eligible participants, participant rates and retention rates	Number identified by HCPs	<50 identified	50–100 identified	100–128 identified	>128 potentially eligible identified	End of recruitment
	Number expressing interest	<30 express interest	30–40 express interest	40–60 express interest	>60 express interest	End of recruitment
	Number providing consent	<15 provide consent	15–25 provide consent	25–30 provide consent	30 provide consent	End of recruitment post-intervention, 3 and 6 months post-intervention
	Number lost to follow up	Attrition >75%	Attrition 50–75%	Attrition 30–50%	Attrition <30%	

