### Sample size

This study aims to assess the feasibility of recruitment processes including the number of eligible participants and participation/retention rates. Papers considering sample size for feasibility and pilot studies suggest the inclusion of upwards of 24–50 participants [59, 90, 91]. The present study aims to recruit 30 patients to participate in three groups of 10 patients each. In order to obtain sufficient data on the intervention, randomisation will be imbalanced so that 20 are randomised to the treatment arm and 10 to the wait-list control group.

Studies of wider psychosocial and psychotherapeutic interventions for chronic depression show participation rates in the range of 25–33% of eligible patients consenting to participate in the study [92–94]. With a sample size of 30, we will be able to estimate a participation rate of 25% to within a 95% confidence interval of +/-15%. Assuming that one fifth of patients accessing primary care for depression will have developed chronic depression, we estimate approximately 1300 patients within primary care will be eligible for this study. We estimate each practice will have around 100 patients with depression, of which around 20 will have enduring symptoms. Within the secondary care sites in which we plan to recruit, there are currently around 1960 patients with a diagnosis of depression. Assuming that one fifth will have developed chronic depression [1], we estimate approximately 392 patients within secondary care will be eligible for this study. Based on a participation rate of 25%, we plan to approach 128 patients with the aim of recruiting 4 per week, over 8 weeks.

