#### Clinical outcomes

This study will employ intention-to-treat analysis. Data from all subjects will be included in the analysis as randomised. Adverse events will be reported by sub-groups of those who were currently receiving the intervention and those who were not.

We will first calculate a mean value of the outcome for each unit and present them with confidence intervals. Outcomes will be compared between intervention and control groups using linear regression models, adjusting for the baseline score of the given outcome. The confidence limits of each treatment effect and knowledge of the clinically important difference (where this is available) will be used to determine whether clinically important differences are ruled out by these confidence limits. The intra-cluster correlation coefficient will be calculated. Due to the small sample size, this estimate is likely to be imprecise, therefore we will also use estimates in the literature from similar studies for comparison to inform the design of any future studies. We will descriptively explore in sub-group analyses whether there are any differences between compliant and non-compliant attenders, responders and non-responders and whether any socio-demographic and clinical characteristics are associated with outcomes. As a preliminary economic evaluation, we will calculate the cost of delivery of music therapy and cost of services received by both groups using the CSRI [83]. This will be descriptive only to provide an estimate for future studies.

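### All 30 participants are randomised at once with baseline scores in hand, but the 20:10 allocation does not use baseline severity; ranked triplets would give better balanced arm summaries at very little cost.

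*Protocol article*

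**What the plan says.** The Randomisation section sets the order of conduct: "Randomisation will occur once all 30 participants have been recruited and baseline measures have been completed". The method is then given as "we will utilise simple block randomisation with unbalanced allocation", with totals of 20 for group music therapy and 10 for the wait-list. Someone outside the study team generates the allocation. No baseline factor enters it.

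Other sections bear on the point:

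- **Outcome.** Under Estimation and appropriateness of outcomes: "Our proposed primary outcome is symptoms of depression, measured by an observer-rated scale", namely the MADRS.
- **Objectives.** Aims and objectives lists "an estimate of the control group mean to ensure change is feasible" among the things to be learned. Table 1 names the control mean and the SD of change as the method for judging the outcome measures.
- **Analysis.** The Clinical outcomes section first presents means with confidence intervals, then compares the arms "using linear regression models, adjusting for the baseline score of the given outcome".
- **Numbers.** The Sample size section says: "The present study aims to recruit 30 patients to participate in three groups of 10 patients each".
- **Emphasis.** Under Outcome measures and endpoints: "Our primary interest is in the feasibility of the trial design and intervention".

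**The concern.** In most trials patients are randomised one at a time, and balancing on a baseline score needs strata or minimisation, with some risk of predictable assignments. Here neither difficulty arises. All baseline MADRS scores exist before the single allocation is drawn, and nobody can be enrolled afterwards in response to it. The plan has this information and does not use it.

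The loss matters most where the numbers are smallest. The control arm has 10 people, and its mean is meant to inform the design of a full trial. If those 10 happen to be unusually severe or mild at entry, the raw control mean and any raw comparison of arm means carry that accident forward.

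**Working it through.** The plan states no figure for baseline balance, so there is none to reproduce.

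**Inputs.** From the document: 30 participants, fixed totals of 20 and 10, one batch, baseline-adjusted linear regression. Assumed: normally distributed baseline scores with SD 1; baseline-outcome correlation r of 0.3, 0.5 or 0.7; 0.5 SD as the mark of a sizeable imbalance.

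**1. Chance imbalance as planned.** The SD of the difference in baseline means is sqrt(1/20 + 1/10) = 0.387 SD. The probability of a difference larger than d is 2 × (1 − Φ(d / 0.387)):

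| d (SD units) | Probability |
|---|---|
| 0.4 | 30% |
| 0.5 | 19.7% |
| 0.6 | 12% |
| 0.75 | 5.3% |
| 1.0 | 1.0% |

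A simulation of 100,000 batches gives 19.6% at 0.5 SD. Block size is irrelevant: blocks that are not ordered by baseline score leave the same figure.

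**2. With triplets ranked on MADRS, one of three to control.** In the same simulation the SD of the difference falls to 0.088. No batch exceeded 0.5 SD, and the chance of exceeding 0.25 SD falls from 52% to 0.6%. A cruder split at the median would leave 3.7% above 0.5 SD.

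**3. The adjusted comparison.** In simulated trials already imbalanced by more than 0.5 SD, the baseline-adjusted effect shifts by no more than about 0.01 SD. The unadjusted difference shifts by 0.21 to 0.48 SD for r from 0.3 to 0.7. For precision, the average variance inflation from chance imbalance is 1.038 as planned and 1.002 with triplets; sqrt(1.038 / 1.002) = 1.018, about 2% in standard error. At an imbalance of exactly 0.5 SD, the squared correlation between arm and baseline is 0.5² × (20 × 10 / 30) / 29 = 0.0575, so the inflation is 1 / (1 − 0.0575) = 1.061, or 3% in standard error.

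**4. The control mean.** As planned, its variance is 1/10 = 0.100 whatever r is. With triplets, the baseline part is the variance of the overall mean plus that of the control arm's departure from it: 1/30 + (2/3)² × 0.088² = 0.0333 + 0.0034 = 0.0368 after rounding. The outcome variance is r² × 0.0368 + (1 − r²) × 0.1:

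| r | Variance with triplets | Reduction |
|---|---|---|
| 0.3 | 0.0943 | 6% |
| 0.5 | 0.0842 | 16% |
| 0.7 | 0.0690 | 31% |

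Simulation gives 6%, 15% and 30%.

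**5. Does the printed interval narrow?** No. An ordinary one-sample 95% interval for the 10 controls uses the within-arm SD, which triplets do not reduce. Its mean half-width is 0.694 SD as planned and 0.703 with triplets at r = 0.5 (0.696 and 0.709 at r = 0.7). Its coverage rises to 96.6% and 98.0%. The gain is real but shows only if the arm means are taken from the baseline-adjusted model.

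**6. Matching the two therapy groups as well.** If each triplet also supplied one member to each therapy group, an unadjusted intra-cluster correlation would be pushed down. With a true value of zero, the average estimate is about −0.008 without matching, but −0.029 at r = 0.5 and −0.051 at r = 0.7 with it.

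**The case against.** The strongest reply is that nothing here is wrong. Fixed totals drawn by an independent researcher are a legitimate design, the trial is about feasibility, and the one comparison that could mislead is already adjusted for baseline. All of that stands. The remaining gain in the treatment effect is about 2% in standard error.

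Several stronger readings are tempting and should be resisted:

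- **That allocation is unrestricted.** It is not: the totals are fixed at 20 and 10. It is unrestricted only with respect to baseline severity.
- **That a 1 in 5 risk threatens the treatment comparison.** The Clinical outcomes section adjusts for the baseline score, which removes the bias. The 1 in 5 also depends on the 0.5 SD cut-off, which is not in the document.
- **That the triplets should also form the two therapy groups, to help the intra-cluster correlation.** The document does not say how the 20 are divided, so no imbalance between those groups can be attributed to the plan. Matching them would bias an unadjusted estimate downwards. The plan already concedes that this estimate will be imprecise.
- **That the change costs nothing.** Triplets balance MADRS and measures related to it, not all eleven clinical outcomes, and ordinary arm-mean intervals become slightly conservative.

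The reply does not dispose of the raw arm means and the control mean. They are planned outputs, the latter is an objective in its own right, and the regression covariate does not reach them unless adjusted means are reported.

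**Conclusion.** The point holds as a cheap, modest improvement. The plan leaves about a 20% chance of a baseline MADRS difference above 0.5 SD when it already holds the data to make that chance practically nil. The adjusted treatment effect is unbiased either way and gains about 2% in standard error. The main benefit is to the control mean, whose variance falls by roughly 6% to 30%, and to the comparability of the raw arm summaries.

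These sizes assume normal baseline scores, correlations of 0.3 to 0.7 that the document does not supply, and a full batch of 30 randomised together as stated.

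**What to change.** In the Randomisation section, replace the description of the method with: the 30 participants are ranked on baseline MADRS and formed into 10 consecutive triplets; within each triplet the independent researcher randomly assigns one participant to wait-list and two to the intervention. This gives exactly 20 and 10. If recruitment does not reach a multiple of three, randomise the incomplete last set with the same 2:1 probabilities.

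Keep the baseline score as covariate, and report arm means from the adjusted model so that their intervals reflect the balance obtained. Divide the 20 intervention participants into therapy groups without matching on severity.

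The cost is a sentence or two of text and a list of identifiers with MADRS scores for the independent researcher. The method depends on the single-batch randomisation already planned.

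The Trial status section puts the start of the intervention in mid to late November 2016. If allocation has already been made, the remaining step for this trial is to report baseline-adjusted arm means. The allocation method can then be carried into the full-trial protocol wherever participants are randomised in batches.

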### Blinding

Blinding of participants and therapists is not possible due to the study intervention and timing of assessments. Researchers conducting follow-up assessments will be blind to participant allocation. An independent statistician will conduct the initial analysis of the main outcomes Due to the unbalanced design it will not be possible to blind the statistician to the treatment allocation.

### Outcome measures and endpoints

Our primary interest is in the feasibility of the trial design and intervention. A summary of the main feasibility outcomes, success criteria and timing is shown in Table 1. Proposed clinical outcomes are:

**Table 1 Tab1:** Methods and timing for assessing, recording and analysing outcome parameters

Outcome	Method	Success criteria				Timing
		Stop	Continue, modify protocol	Continue without modification but monitor closely	Continue without modifications	
Acceptability of methodology	Recruitment and retention rates as below					End of recruitment (week 8)
	Compliance	Mean attendance <10 sessions	Mean attendance <14 sessions	Mean attendance 14 sessions	Mean attendance 14+ sessions	End of intervention (week 22)
	End interviews	Unfavourable views, serious concerns	Unfavourable views, suggestions for modification	Favourable views, suggestions for modification	Favourable views, no concerns	1 month post-intervention (week 26)
Feasibility of recruitment processes	Screening rates	Identify <50 potentially eligible subjects	Identify <100 potentially eligible subjects	Identify 100–128 potentially eligible subjects	Identify >128 potentially eligible subjects	End of recruitment
	Recruitment rates	Recruit <50% of sample size	N <25 in 8wks, <5% per week	*N* = 25–30 in 8wks, <13% per week	*N* = 30 in 8wks, 13% per week or greater	End of recruitment
	Participation rates	Participation rate <5%	Participation rate 5–15%	Participation rate 15–25%	Participation rate 25% or greater	6 months post-intervention
	Retention rates	Attrition >75%	Attrition 50–75%	Attrition 30 − 50%	Attrition <30%	6 months post-intervention
	End interviews	N/A	Major suggestions to improve recruitment processes	Minor suggestions to improve recruitment processes	No suggestions to improve expressed	1 month post-intervention (week 26)
Identify number of eligible participants, participant rates and retention rates	Number identified by HCPs	<50 identified	50–100 identified	100–128 identified	>128 potentially eligible identified	End of recruitment
	Number expressing interest	<30 express interest	30–40 express interest	40–60 express interest	>60 express interest	End of recruitment
	Number providing consent	<15 provide consent	15–25 provide consent	25–30 provide consent	30 provide consent	End of recruitment post-intervention, 3 and 6 months post-intervention
	Number lost to follow up	Attrition >75%	Attrition 50–75%	Attrition 30–50%	Attrition <30%	
Researcher time and costs per participant	Researcher diary	N/A	Researcher time exceeds allocated time requiring additional study support	Researcher time and cost only just covers time required	Researcher time and cost fully covers time required	6 months post-intervention
Appropriate outcome measures	Variability of outcome Estimate of control mean and SD of change	No difference or clinically important difference favouring control detected based on confidence limits	Difference cannot be detected based on confidence limits but data suggest improvement favouring intervention	Difference can be detected based on confidence limits	Clinically important difference can be detected based on confidence limits	End of intervention
Intervention components	Therapist adherence	Adherence <50%	Adherence <50%	Adherence 50–75%	Adherence >75%	End of intervention
	End interviews	Serious concerns expressed regarding intervention	Major suggestions to adapt intervention	Minor suggestions to adapt intervention	No concerns or suggestions to adapt intervention	
Intervention adherence	Therapist self-rated adherence Video-rated adherence	Adherence <25%	Adherence 25–50%	Adherence 50–75%	Adherence >75%	End of intervention
Estimate of cost of intervention and services received	Therapist time CSRI	Cost significantly greater than usual care, no potential to modify intervention, no indication of benefits	Cost is greater than usual care - intervention may be modified, but outcomes suggest some benefits	Cost is greater than usual care but outcomes strongly suggest benefits	Cost is equivalent to or slightly greater than usual care, outcomes strongly suggest benefits	6 months post-intervention

*HCPs* healthcare professionals, *N/A* not applicable, *CSRI* Client Services Receipt Inventory

Observer rated:Symptoms of depression as measured by the Montgomery-Åsberg Depression Rating Scale (MADRS) [62, 66, 67]Social functioning as measured by the life skills profile (LSP) [68]Level of hospitalisation as measured by admission, length of stay and number of readmissions

Self-report:4.Self-reported symptoms of depression as measured by the Beck Depression Inventory II (BDI-II) [69–71]5.Psychological distress as measured by the Brief Symptom Inventory (BSI) [72]6.Self-esteem as measured by the Rosenberg Self-Esteem Scale (RSES) [73–75]7.Perceived self-efficacy as measured by the General Perceived Self-Efficacy Scale (GPSES) [76–78]8.Satisfaction with treatment in community services as measured by the Client Satisfaction Questionnaire (CSQ) [79]9.Work and social adjustment as measured by the Work and Social Adjustment Scale (WSAS) [80]10.Quality of life as measured by the Manchester Short Quality of Life Scale (MANSA) [81, 82]11.Receipt of services as measured by the Client Services Receipt Inventory (CSRI) [83, 84]

Our proposed clinical endpoint is the week post-intervention, with secondary endpoints at 3 and 6 months post-intervention. Process measures of attendance, self-reported depression symptoms (BDI-II [69]) at weeks 3, 6 and 9 and weekly mood pre-session and post-session (Dispositional Mood Scale (DMS) [85, 86]) and group relationships (Relationship Satisfaction Scale (RSS) [87]) will be measured.

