### Statistical analysis

#### Feasibility

As this is a feasibility study, the main statistical reporting will comprise descriptive statistics and calculation of effect sizes. We will assess:• Acceptability of methodology to professionals and patients through interviews via recruitment rates, compliance, end interviews      • Feasibility of recruitment processes• Deviation around specific post-intervention, and 3-month and 6 month post-intervention follow-up assessment dates for actual data collection• Number of eligible participants, participation rates and retention rates• Researcher time and costs per participant• Appropriateness of outcome measures

Descriptive analyses will establish recruitment and drop-out rates and the distribution of baseline characteristics and all outcomes post-intervention, and 3 months and 6 months post-intervention. The research team will reflect upon the representativeness of the demographics in terms of the general population of patients that could potentially be useful in assessing the intervention.

Recruitment and drop-out rates will be monitored on a monthly basis allowing for examination and reporting of patterns and whether there are any obvious trends. This may inform the choice of the primary outcome for a full-scale trial allowing for drop-outs in a sample-size calculation.

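### In Table 1's recruitment-rate row, the 5% weekly threshold for modifying the protocol does not match its own count of 25 and lies inside the Stop zone

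*Protocol article*

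**What the plan says.** The recruitment-rate row of Table 1 (protocol article, Outcome measures and endpoints) has four verdicts and is scored at the end of recruitment:

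- Stop: "Recruit <50% of sample size".
- Modify the protocol: "N <25 in 8wks, <5% per week".
- Continue, but monitor closely: N = "25–30 in 8wks, <13% per week".
- Continue without modification: N = "30 in 8wks, 13% per week or greater".

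The last three cells each pair an 8-week count with a weekly percentage. The article does not say what the percentage is a share of, whether both parts of a cell must be met, or which part prevails if they differ.

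The Sample size section supplies the figures needed to read the row: "The present study aims to recruit 30 patients to participate in three groups of 10 patients each", and "we plan to approach 128 patients with the aim of recruiting 4 per week, over 8 weeks". A later row of the same table, on the number of patients who consent, uses counts only: fewer than 15, 15–25, 25–30, and 30.

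**The concern.** A count over a fixed 8-week window and a weekly rate are the same quantity on two scales, so the two halves of a cell should convert into each other. In the top cell they do, to the rounding used. In the modify cell they do not: a rate of 5% per week is about half of what 25 recruits in 8 weeks requires, and it is below the row's own Stop limit.

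Recruitment feasibility is one of the trial's listed objectives, and this row is a pre-set rule for judging it. The range affected is 15 to 24 recruits, or 50% to 80% of target. There the row can be read as calling for a changed protocol or for an unchanged one under close monitoring. If the wording leaves that open, the choice can be made after the count is known, which pre-set criteria are meant to prevent.

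**Working it through.** **Inputs.** Target sample 30, pace 4 per week, window 8 weeks and 128 patients to approach (Sample size). Stop limit 50% of the sample, and the paired counts and percentages (Table 1, recruitment-rate row).

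**Step 1. Find the denominator by reproducing the printed 13%.**

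- Share of the target sample: planned pace 4 / 30 = 13.3%; 30 recruits in 8 weeks is 30 / 8 / 30 = 12.5%. Both give 13% in whole percentages. In reverse, 0.13 × 30 × 8 = 31.2, close to 30.
- Share of 32 (4 × 8, also 25% of 128): 4 / 32 = 12.5%, also near 13%.
- Share of the 128 approached: 0.13 × 128 × 8 = 133 recruits, more than the number approached, so this is not possible.

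The sample of 30 is therefore the natural denominator and 32 the only workable alternative.

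**Step 2. Convert the 5%.**

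- On 30: 0.05 × 30 × 8 = 12.0 recruits.
- On 32: 0.05 × 32 × 8 = 12.8 recruits.

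The Stop limit is 0.50 × 30 = 15 recruits. On either denominator, every result below 5% per week is already a Stop.

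**Step 3. Convert the counts, with weekly percentage = N / (8 × 30) = N / 240.**

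- 15 / 240 = 6.25%
- 24 / 240 = 10.0%
- 25 / 240 = 10.4%
- 29 / 240 = 12.1%
- 30 / 240 = 12.5%

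The rate that belongs with 25 recruits is 10.4%. The printed 5% is about half of that, so rounding does not explain it. On 32 the rate would be 25 / 256 = 9.8%, with the same conclusion.

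**Step 4. Classify each result under the possible readings (denominator 30).**

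| Recruits in 8 weeks | Weekly % | By count | By weekly percentage | Both parts required |
|---|---|---|---|---|
| Below 12 | Below 5.0 | Stop | Modify | Stop |
| 12–14 | 5.0–5.8 | Stop | Monitor | Stop |
| 15–24 | 6.25–10.0 | Modify | Monitor | No cell |
| 25–29 | 10.4–12.1 | Monitor | Monitor | Monitor |

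The readings agree for 25–29. They part for 15–24, which is the whole band that the counts assign to modify.

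**The case against.** The strongest defence is that the counts settle the matter. Table 1 uses nested cut-offs elsewhere (attendance below 10, then below 14; screening below 50, then below 100). Read left to right with the worst matching verdict applying, the row gives Stop below 15, modify for 15–24 and monitor for 25–29. The 5% is then redundant and changes nothing. The consent row repeats the count bands without any percentage, which shows which half of the cell was meant. A result of 15–24 also fails the count in the monitor cell, so it reaches that verdict only if half the cell is ignored.

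Most of this stands, and it limits what can be claimed:

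- A reader might infer that the modify verdict is empty and also that 12 to 24 recruits receive contradictory verdicts. These do not hold together as fact. The verdict is empty only if the percentage binds; two verdicts arise only if count and percentage are separate, equal rules; under the joint reading, 15–24 gets no verdict. For 12–14 the Stop cell is plainly met and carries no weekly rate.
- A reader might infer that a design recruiting half to 80% of target would go forward unchanged. The team would have to set aside both the count in this row and the consent row to do that.
- A reader might see further errors nearby, and the documents do not support them. Planning 4 per week for 8 weeks gives 32, which is 25% of 128 and a slight surplus over 30. The step from 12.5% to 13% is rounding. Monthly monitoring does not prevent scoring, because the row is scored at the end of recruitment, when the average weekly rate is the total divided by 8.

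The defence does not remove the printed error. The nested reading works only by disregarding the 5%, and the article does not tell the reader to do so.

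**Conclusion.** The point holds for one threshold. The 5% weekly figure corresponds to 12 recruits (12.8 on a denominator of 32), not 25, and lies wholly below the row's Stop limit of 15. Applied as printed, it moves 15–24 recruits from modify to monitor, or leaves them without a verdict.

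The conclusion rests on one inference: that the percentage is a share of the target sample. The article does not state this, but the 13% supports it, and the alternative of 32 leads to the same result.

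Severity is minor to moderate. The row is one of several progression criteria in a feasibility trial of 30 with mainly descriptive reporting, and no hypothesis test or effect estimate depends on it. The consent row points to the intended bands. It is still a wrong decision threshold on a stated objective and should be corrected before the row is used. The shared end-point at 30, which sits in both the monitor and the continue cells, is cosmetic and can be tidied in the same edit.

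**What to change.** State that the weekly percentage is a share of the target sample of 30, and put the row on one non-overlapping scale that follows the counts:

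| Verdict | Recruits in 8 weeks | Weekly % of 30 |
|---|---|---|
| Stop | Fewer than 15 | Below 6.25 |
| Modify | 15–24 | 6.25–10.0 |
| Monitor closely | 25–29 | 10.4–12.1 |
| Continue | 30 within 8 weeks | 12.5 or more |

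The gaps between the percentage bands are harmless, because no whole number of recruits falls in them. Use the same cut-offs in the consent row, where 25 and 30 now each belong to two bands. Dropping the percentages and keeping the counts alone would serve equally well.

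The cost is a correction to two table rows and one clause naming the denominator. It needs no additional data and no change to the conduct of the trial.
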